## Abstract

**Background:**

Cryotherapy (the application of ice for therapeutic purposes) is one of the most common treatment modalities employed in the immediate management of acute soft tissue injury. Despite its widespread clinical use, the precise physiological responses to therapeutic cooling have not been fully elucidated, and effective evidence-based treatment protocols are yet to be established. Intermittent ice applications are thought to exert a significant analgesic effect. This could facilitate earlier therapeutic exercise after injury, potentially allowing for a quicker return to activity. The primary aim of the forthcoming study is therefore to examine the safety and effectiveness of combining intermittent ice applications with periods of therapeutic exercise in the first week after an acute ankle sprain.

**Methods/Design:**

The study is a randomised controlled trial. 120 subjects with an acute grade I or grade II ankle sprain will be recruited from Accident & Emergency and a University based Sports Injury Clinic. Subjects will be randomised under strict double-blind conditions to either a standard cryotherapy (intermittent ice applications with compression) or cryokinetic treatment group (intermittent ice applications with compression and therapeutic exercise). After the first week, treatment will be standardised across groups. Assessor blinding will be maintained throughout the trial. Primary outcome will be function, assessed using the Lower Extremity Functional Scale (LEFS). Additional outcomes will include pain (10 cm Visual Analogue Scale), swelling (modified figure-of-eight method) and activity levels (*activ*PAL™ physical activity monitor, PAL Technologies, Glasgow, UK). Diagnostic Ultrasound (Episcan-1-200 high frequency ultrasound scanning system, Longport International Ltd, PA) will also be used to assess the degree of soft tissue injury. After baseline assessment subjects will be followed up at 1, 2, 3 & 4 weeks post injury. All data will be analysed using repeated measures analysis of co-variance (ANCOVA).

**Discussion:**

This paper describes the rationale and design of a randomised controlled trial which will examine the effectiveness of two different cryotherapy protocols in the early management of acute ankle sprain.

**Trial Registration:**

ISRCTN13903946

## Background

Ankle injuries represent one of the most commonly occurring musculoskeletal complaints. The vast majority of such injuries occur as a result of inversion trauma with the foot in some degree of plantar flexion and involve damage to the lateral structures of the ankle. Sprains of the lateral ankle ligaments are associated with significant costs [1] and account for an estimated 302,000 annual admissions to Accident & Emergency (A&E) Departments in the UK [2].

In addition to the immediate onset of pain, swelling and loss of joint motion, it has been reported that in 15 – 73% of cases, chronic ankle instability (CAI) with recurrent sprains and residual sensations of giving way may occur following lateral ankle sprain [3,4]. However, the precise etiology of CAI is unclear and as a consequence the optimal intervention for the management of acute ankle sprain is controversial. While a significant body of evidence supports the use of early functional treatment [5-7], there is little high quality research evidence to suggest which interventions best augment this treatment approach. Clinicians therefore continue to treat such injuries pragmatically, with current recommendations ranging from no intervention to physiotherapy referral, prophylactic bracing, or cast immobilisation [8-11].

Cryotherapy (the application of ice for therapeutic purposes) is a common treatment modality employed in the management of acute soft tissue injuries. Despite its widespread clinical use, the precise physiological responses to ice application have not been fully elucidated. Moreover, the rationale for its use at different stages of recovery is quite distinct. In the acute inflammatory phase after soft tissue injury, cryotherapy is thought to decrease oedema formation via induced vasoconstriction, and reduce secondary hypoxic damage by lowering the metabolic demand of injured tissues [12,13]. Cooling skin surface temperature to below approximately 15°C is also thought to exert a localised analgesic effect by inhibiting nerve conduction velocity [14,15]. Short periods of ice application have been used during the later, sub-acute phase of inflammation to produce a similar analgesic effect, thus facilitating earlier and more aggressive therapeutic exercise after muscle injury [16,17]. This combined use of cryotherapy and exercise has previously been termed *cryokinetics *[18]. Recent evidence has suggested that the addition of exercise to ice application is more effective than ice application alone after various soft tissue injuries, including acute ankle sprain [19]. However, by reducing the conduction velocity of other, non-nociceptive fibres, cold application may also have a number of deleterious effects, including reduced muscle torque [20]. This is of particular relevance if ice is to be applied in combination with therapeutic exercise in the early stages after an acute soft tissue injury. Such effects could lead to the development of altered neuromuscular control patterns and potentially, to an increased risk of re-injury. Conversely, other evidence has shown that ice application does not negatively affect myotatic reflex activity [21], joint position sense [22], plantar flexion torque [23] or more functional measures of agility [24,25]. Such conflicting findings may relate to the marked variation in cryotherapy protocols described in the literature, particularly in relation to the site, mode and duration of ice application. These factors, in addition to the level of subcutaneous fat, dictate the degree of superficial and deep tissue cooling, and therefore have a direct effect on the subsequent physiological response to cryotherapy [26].

Evidence from a large-scale systematic review suggested that intermittent ice applications of 10 minutes are most effective at reducing tissue temperature in both injured animal and healthy human models [27]. Such ice applications have been shown to reduce skin temperature to 5°C immediately after treatment [28]. A recent study by our research group also found that intermittent ice applications are more effective than continuous ice at reducing pain on activity after ankle sprain [29].

Given these findings, it seems a logical progression to examine if the analgesic effects of intermittent ice application can facilitate earlier therapeutic exercise, and subsequently improve clinical outcome following acute ankle sprain. The safety and effectiveness of incorporating therapeutic exercise with periods of intermittent ice application has not previously been examined in patients with acute soft tissue injury. The primary aim of the forthcoming trial is therefore to compare the effectiveness of standard intermittent versus cryokinetic ice applications in the management of acute grade I and grade II ankle sprains. In this manner we hope to contribute further to the existing evidence base in the area of acute soft tissue injury management.

## Methods/Design

The study is a randomised controlled trial (RCT). Figure 1 shows a brief summary of the trial design. The primary trial site will be the A&E Department of the Royal Victoria Hospital, Belfast, Northern Ireland. Subjects will also be recruited from the Sports Injury Clinic at the University of Ulster, Jordanstown, Northern Ireland. Following guidelines set out in the CONSORT statement [30], the number of patients assessed, randomised to treatment groups, who complete the study and who are included in the final analysis of the primary outcome shall be recorded during the trial. This will enable a participant flow diagram to be constructed. Ethical approval for the trial has been granted by The University of Ulster Research Ethics Committee [National Research Ethics Service reference number: 06/NIR03/148]. All patients who agree to take part will be required to give informed written consent prior to participation in the study.

**Figure 1 F1:**
[figure not shown]
Summary of trial design.

### Study population

All patients between 16–65 years with an acute lateral ankle sprain (less than 1 week since injury) will be considered for participation in the study.

### Identification of potential subjects

Following initial assessment by an attending clinician (Emergency Nurse Practitioner, Physiotherapist or Doctor) patients with a suspected ankle sprain will be approached by a member of the research team and given a brief verbal explanation of the study. They will then be provided with a detailed study information sheet to consider while awaiting routine x-ray. This will allow for a standard 'cooling off' period of at least 1 hour.

### Inclusion/exclusion criteria

Patients with an acute grade I or grade II sprain will be included in the trial on the basis of a standard physical examination of the acutely injured ankle. As part of this assessment, the following demographic information will be recorded: date of birth, height, mass, gender, limb dominance and occupation. Activity level prior to injury will also be recorded and used to group patients according to whether they are from an athletic (defined as participating in high-intensity exercise for more than 90 minutes at least 3 times per week) or non-athletic population.

Patients will be excluded if any of the following criteria are present: Complete (Grade III) ankle ligament rupture (mechanical instability diagnosed by a positive anterior drawer or inversion stress test); Bony ankle injury (indicated by Ottawa ankle rules [31] or plain x-ray); Multiple injuries (e.g. other joint injury or fracture); Ankle sprain more than 1 week since injury; Any contraindication to cryotherapy including cryoglobinaemia, peripheral vascular disease or Raynaud's syndrome. Subjects will also be excluded if they are non-English speaking, have any condition which will affect understanding and communication, are under the influence of drugs/alcohol, or if there is no sufficient address given for follow-up.

### Baseline outcome measurements

Baseline recording of all outcome measures shall be carried out by the same researcher prior to randomisation.

#### Primary outcome measure

i) Subjective ankle function, assessed using the Lower Extremity Functional Scale (LEFS) [32]. The LEFS is an 80 point scale which has been shown to have excellent test-retest reliability (intraclass correlation coefficient [ICC] = 0.94, 95% confidence interval [CI] lower limit = 0.89). The scale has a potential error of ± 5.3 points (90% CI), with a minimal detectable change (MDC) and minimal clinically important difference (MICD) of 9 points (both 90% CI).

#### Secondary outcome measures

ii) Pain assessed using a 10 cm visual analogue scale, marked "no pain" at one end and "worst pain imaginable" at the other. This form of assessment is considered most appropriate because of its high level of repeatability when used serially on the same patient [33].

iii) Swelling assessed using a modified version of the figure-of-eight method [34]. High intra and inter-rater reliability has been reported using this technique (ICC = 0.99, 95% CI lower limit = 0.98), MDC = 9.6 mm (95% CI). To determine the degree of swelling, the mean value (of 2 measures) will be subtracted from the mean value of the uninjured ankle.

iv) Physical activity levels assessed using the *activ*PAL™ professional physical activity logger (PAL technologies, Glasgow, UK). Reported ICCs for inter-device reliability range from 0.79–0.97 (CIs not stated) [35]. The *activ*PAL™ unit (5 cm × 3 cm) will be worn on the thigh of the injured leg, for one week post injury. Time spent sitting, standing and walking under free living conditions will be compared between groups.

#### Tertiary outcome measure

v) Diagnostic ultrasound scanning (Episcan-1-200 high frequency ultrasound scanning system, Longport International Ltd, PA) will be used to examine the lateral structures of the injured and uninjured ankle. Images will be used to quantify the degree of soft tissue swelling and identify the relative positions of the fibula and talus (Figure 2). It is anticipated that this will provide a more accurate measure of swelling, and provide a useful tool to guide future clinical studies. For practical reasons, only those subjects who are recruited through the University Sports Injury Clinic will undergo ultrasound scanning.

**Figure 2 F2:**
[figure not shown]
Ultrasound images of lateral ankle. (a) Un-injured control. (b) Grade I sprain 7 days post injury. The hypoechoic zone between the markers (*) indicates an area of soft tissue swelling. F = Fibula. T = Talus. ATFL = Anterior talofibular ligament. [Scale = mm]

### Treatment allocation

A statistician who will have no contact with the day to day running of the trial shall carry out all aspects of preparation for group randomisation. 184 randomisation envelopes will be produced in the following manner: 92 cards will be printed with **Group I (standard ice application)**. 92 cards will be printed with **Group II (cryokinetic ice application)**. Each card will be placed inside an opaque envelope with carbon paper on top. A randomisation sequence will then be generated using computer software. Stratified randomisation will be employed according to whether subjects are from an athletic (A) or non-athletic population (N). Separate block randomisation sequences will be produced for each stratum using an allocation ratio of 1:1 and a block size of 4 to ensure comparison groups are of approximate size. Envelopes for each stratum will be labeled sequentially (1A-92A & 1N-92N). Envelopes will then be sealed and signed across the seal. Following baseline assessment, these instructions, in sequentially numbered opaque sealed envelopes, will be used to assign sequentially enrolled subjects to one of the two treatment groups. Subjects shall therefore be randomised to treatment groups under strictly double-blind conditions. Before opening the envelope, the Research Physiotherapist will write the subjects unique identification number (stratification number & date of birth) on the outside of the envelope, transferring this information to the instruction card. At the end of the trial this will allow the Principle Investigator to check each card against the original randomisation lists and verify that all subjects received the treatment to which they were assigned.

### Treatment protocols

All subjects will receive an initial treatment, administered by the same Research Physiotherapist, in A&E or the University Sports Injury Clinic. Standard treatment (Group I) will consist of intermittent ice and compression only. Subjects will receive a 10 minute ice application. The ice pack will then be removed for 10 minutes before a further 10 minute ice application. This will then be followed by a further 10 minutes of rest (10 minutes ice/10 minutes rest/10 minutes ice/10 minutes rest). Cryokinetic treatment (Group II) will consist of intermittent ice and compression with therapeutic exercise. Subjects will receive a 10 minute ice application. The ice pack will then be removed and the subject will perform 10 minutes of therapeutic exercise. This will be followed by another 10 minute ice application and a further 10 minutes of therapeutic exercise (10 minutes ice/10 minutes exercise/10 minutes ice/10 minutes exercise). Subjects will be responsible for ice pack preparation and self administering subsequent treatments at home (3 times per day for the first week after injury). Compliance with treatment and analgesic consumption will be monitored by the use of a treatment diary. Standard advice regarding general mobilisation exercises and weight bearing will also be given to both groups according to routine A&E practice.

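### Sprains up to a week old may enter and visits are timed from injury, yet the analysis adjusts only for the baseline value and not for days since injury

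*Protocol article*

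**What the plan says.** All places are in the protocol article.

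- **Entry window.** Study population: a patient with an "acute lateral ankle sprain (less than 1 week since injury) will be considered for participation". The exclusion list removes only an "Ankle sprain more than 1 week since injury".
- **Randomised treatment.** Treatment protocols: one supervised session at entry, with patients then "self administering subsequent treatments at home (3 times per day for the first week after injury".
- **End of the treatment contrast.** Abstract, Methods/Design: "After the first week, treatment will be standardised across groups". Follow-up procedure & blinding says the same for the period after week 1.
- **Visits.** Abstract, Methods/Design: "After baseline assessment subjects will be followed up at 1, 2, 3 & 4 weeks post injury". Follow-up procedure & blinding also dates the first reassessment from injury.
- **Activity monitor.** Secondary outcome measures: it "will be worn on the thigh of the injured leg, for one week post injury".
- **Analysis.** Statistical analysis specifies a repeated measures ANCOVA with treatment group as the between-subject factor, weeks 1 to 4 as the within-subject factor, and the baseline value, called week 0, as the only covariate.
- **Stratification.** Treatment allocation stratifies by athletic status, not by time since injury.

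**The concern.** The entry window and the visit clock both start at the injury, and both last a week. A patient's entry day therefore fixes how much of the first week is left for treatment and how much time passes before the first outcome visit. Calling every baseline week 0 hides this.

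The baseline covariate does part of the work, because a patient seen later has usually recovered further and the score reflects that. It cannot do all of it. Take two patients with the same baseline score, one seen on the day of injury and one on day 6. The first has about a week of recovery ahead before the week 1 visit and the second about a day. Their expected week 1 scores differ, and a model that knows only the baseline score puts that difference into the residual.

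What is at stake is precision, mainly at week 1, where the intervals differ most in relative terms.

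**Working it through.** **Inputs from the protocol article.** Entry on day *d* = 0 to 6 after injury (Study population). One supervised session plus three home sessions a day to the end of week 1 after injury (Treatment protocols). Two 10-minute exercise periods per session in the cryokinetic arm, so 20 minutes (Treatment protocols). Visits at 7, 14, 21 and 28 days after injury (abstract). 120 patients with 10% attrition (abstract; Sample size).

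The plan gives no figure of its own for entry delay, so there is none to reproduce.

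**Step 1: exposure and intervals by entry day.** Treatment days = 7 − *d*; sessions = 1 + 3(7 − *d*); exercise minutes = 20 × sessions; baseline to week 1 = 7 − *d*; baseline to week 4 = 28 − *d*. Full adherence is assumed.

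| Entry day | Sessions | Exercise, cryokinetic arm (min) | Baseline to week 1 (days) | Baseline to week 4 (days) |
|---|---|---|---|---|
| 0 | 22 | 440 | 7 | 28 |
| 1 | 19 | 380 | 6 | 27 |
| 2 | 16 | 320 | 5 | 26 |
| 3 | 13 | 260 | 4 | 25 |
| 4 | 10 | 200 | 3 | 24 |
| 5 | 7 | 140 | 2 | 23 |
| 6 | 4 | 80 | 1 | 22 |

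The interval to week 1 varies sevenfold. The interval to week 4 varies by 28/22, or about 1.3-fold.

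**Step 2: what the extra covariate costs and gains.** Patients analysed: *n* = 120 × 0.90 = 108. With *k* covariates the expected variance inflation of the treatment estimate is (*n* − 3)/(*n* − *k* − 3).

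- *k* = 1 (as planned): 105/104
- *k* = 2 (with delay): 105/103

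If delay explains a share *R*² of the variance left after the baseline value, the variance ratio of the new analysis to the planned one is (104/103)(1 − *R*²). The change in standard error is the square root of that ratio minus 1. The equivalent number of patients is 108/ratio − 108.

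| Assumed *R*² | Variance ratio | Change in SE | Equivalent patients |
|---|---|---|---|
| 0 | 1.0097 | +0.5% | −1.0 |
| 0.01 | 0.9996 | 0.0% | 0.0 |
| 0.02 | 0.9895 | −0.5% | 1.1 |
| 0.05 | 0.9592 | −2.1% | 4.6 |
| 0.10 | 0.9087 | −4.7% | 10.8 |

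Break-even is at *R*² = 1 − 103/104, just under 1%. The document gives nothing from which *R*² could be derived, so the range is an assumption.

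**The case against.** The strongest reply is that the injury clock is deliberate and sound. The stated aim concerns "combining intermittent ice applications with periods of therapeutic exercise in the first week after an acute ankle sprain". Treatment defined as first-week care ends naturally on day 7, and visits at fixed times after injury compare patients at the same point of recovery. This stands: the clock is a legitimate design choice and is used consistently.

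A second reply is that delays will be short, since patients are approached at their clinical attendance and "provided with a detailed study information sheet to consider while awaiting routine x-ray". Many probably attend soon after injury, but the article does not say how soon, and a one-week window was chosen. The reply limits the likely size and does not remove the point.

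A third is that an extra covariate is a matter of preference, because the baseline value already carries much of the delay. That holds if delay explains less than about 1% of what remains. Even then the loss is about 0.5% on the standard error. The covariate set is not simply left open for an analysis plan, because the article names it.

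Several stronger readings are tempting but not supported:

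- **Bias or inflated type I error.** Randomisation balances delay in expectation, so neither follows.
- **A large loss of power, or late entrants adding little contrast.** Either needs a relation between number of sessions and effect, and a power figure needs the spread of entry days as well. The article gives neither.
- **No baseline for activity.** Baseline outcome measurements says all outcomes are recorded before randomisation, and Table 2 assigns baseline recording of activity levels to the blinded assessor.
- **Activity compared as raw totals over unequal wear.** The article says that times will be compared, not that totals will be. A per-day summary is detail that an analysis plan can supply.

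**Conclusion.** The point holds as a minor weakness of the analysis model. As written, entry day changes the baseline-to-week-1 interval from about 7 days to about 1 and the planned sessions from about 22 to about 4, while the model treats all baselines as the same week 0 and adjusts only for their value. The comparison between arms remains valid. Some precision is lost, probably a modest amount; it cannot be quantified without the distribution of entry days and the strength of the link between delay and outcome.

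The conclusion rests on reading the article's injury-based timing literally. If the authors meant timing from enrolment, the unequal intervals disappear, although time since injury would still describe where each patient stands in recovery.

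**What to change.** In Statistical analysis, name two covariates: the week 0 value of the outcome and the number of days from injury to baseline. In the activity model, keep the recorded activity baseline where it exists and add the days from injury beside it. The added term accounts for differences in expected recovery. The treatment effect remains an average over patients with different lengths of exposure.

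The cost is one degree of freedom, at worst about 0.5% on the standard error with 108 analysed. The date of injury is already needed for eligibility and for dating visits, so there are no extra data, patients or visits, and the entry window need not be narrowed.

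Two clarifications would help, though neither corrects an error: confirm that week 1 runs from injury, and state that sitting, standing and walking times are expressed per day of monitor wear. Moving treatment and visits to a clock that starts at randomisation is not needed. It would change the treatment window under study and the stage of recovery at each visit.
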